#### Secondary Outcomes-Neurophysiological

The neurophysiological outcomes include cortical area representation of the finger-hand muscles as measured by Transcranial Magnetic Stimulation (TMS), and brain connectivity as measured through Electroencephalography (EEG). TMS mapping and EEG data will be acquired at pre- and post-therapy and at 4 months post stroke (see Table 2).

**Table 2 T2:** Assessment schedule for the outcome measures.

**Measure**	**Domain measured**	**Pre-test^**^**	**Post-test**	**1 month**	**4 months**	**6 months**
**Primary outcome**						
Action research arm test	Upper limb function	x	x	x	x	x
**Secondary outcomes - clinical**						
Box and blocks	Gross manual dexterity	x	x	x	x	x
Upper extremity fugl-meyer assessment	Upper limb impairment	x	x	x	x	x
Patient's structured assessment	Perception of limb function		x			
EuroQol	Health-related quality of life	x	x	x	x	x
NIH health stroke scale	Neurological status	x				
**Secondary outcomes – kinematic/kinetic**						
Maximum isometric pinch force	Maximum force produced	x	x	x	x	x
Pinch force regulation	Modulation of force production	x	x	x	x	x
Range of motion (ROM)	Active/Passive ROM upper limb	x	x	x	x	x
Real-world reach-to-grasp test	Kinematics of grasping	x	x	x	x	x
Robot based daily kinematic measures	Immediate effects of training	x	x			
Home-based accelerometry	Amount of daily arm use		x^*^		x	
**Secondary outcomes – neurophysiological**						
TMS - MEP amplitude and extent	Patterns of cortical reorganization	x	x		x	
EEG	Resting state/task-based brain connectivity	x	x	x	x	x

* *ideally within 72 h after Post-test*.

** *The delayed VR group has two PRE tests, one in the hospital and one immediately prior to the delayed VR intervention*.

*Patterns of Corticospinal Reorganization* will be assayed using single-pulse TMS (Magstim Rapid with an AirFilm Coil). Changes in the ipsilesional and contralesional hand cortical territory will be quantified using motor evoked potentials (MEPs) in persons that meet specific safety criteria for TMS. The topographic representation of the following hand and arm muscles will be mapped before and after training and at the three retention time points: first dorsal interosseous [FDI], extensor indicis longus [EI], abductor pollicis brevis [APB], abductor minimi [ADM], flexor digitorum superficialis [FDS], extensor digitorum communis [EDC], flexor carpi radialis (FCR), extensor carpi radialis [ECR], extensor pollicis longus [EPL], and brachioradialis [BR]. To ensure spatial precision we will employ frameless neuronavigation (Brainsight, Rogue Research, Inc.).

A threshold of 50 uV will be used to detect MEPs against background EMG (45). MEP amplitude will be measured as the peak-to-peak amplitude of the EMG signal 20–50 ms after the TMS pulse. In addition, the amplitude of the background EMG will be calculated as the area under the EMG envelope in the 50 ms interval before the TMS pulse where the envelope is generated by filtering the signal with 2nd order Butterworth filter (5–250 Hz band-pass), full-wave rectifying the filtered signal and applying 20 Hz low-pass filter. MEP and background EMG amplitude will be estimated for each muscle and for each stimulation point. MEP amplitudes and coordinates of the stimulation points will be interpolated to a 7 × 7 cm mesh of 5 mm resolution centered on the M1 hotspot using cubic surface interpolation method (46, 47). This will allow comparisons across maps and sessions. The weighted-average location of corticospinal output devoted to a muscle, or center of gravity (COG), is expressed as an MEP-weighted centroid of the cortical representation in the rostral-caudal (COGx) and medial-lateral (COGy) plane using standard equations (45, 48).

The product of the number of interpolated scalp sites eliciting MEPs and the map resolution (0.5 mm) represents the extent of the representation producing corticospinal output (MEPs), or map area (47–51). Overall excitation is represented by map volume (also described in the literature as “weight”), (48, 51) and calculated as the integrated amplitude using double trapezoidal integration of interpolated maps (52) across all responsive stimulation sites (51). Map area, volume, and COG have been used extensively to describe sensorimotor cortex reorganization after stroke [for a review see Cortes et al. (53)]. The shift of the COG, enlargement of motor representation area, and the increase in the volume of excitation of the ipsilesional hemisphere have been shown to correlate with functional measures of motor recovery. The total area representing the intrinsic muscles (FDI, EI, ADM, APB) and extrinsic muscles (FDS, EDC, FCR, ECR, EPL, and BR) will be calculated to quantify changes in cortical somatotopy of fine and gross motor muscle groups of the hand, respectively.

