#### Secondary Outcomes - Neurophysiological

For Aim 3, variables will be analyzed with a mixed model, with fixed effects of TEST TIME (Baseline, Post, 1, 4, 6 M), sensorimotor cortex (Ipsilesional, Contralesional), Muscle (Intrinsic, Extrinsic) and Treatment Group (EVR, DVR, DMUC, UC). AREA (size of the cortical surface area in the affected hemisphere where MEPs can be elicited, to be used as an index of focusing of the cortical excitability distribution) will be used as an outcome measure. In addition to group analyses, we will use a Spearman rank order test to correlate individual subject measures of cortical topography (Area/Volume/COG shift, measured by TMS mapping) and clinical measurements of impairment (hand/wrist UEFMA) and function (distal WMFT) across testing time points. In our experience, individual subject data analysis has proven invaluable in understanding the effects of therapy on functional recovery. Non-parametric statistics (Kruskal-Wallis or Mann-Whitney) will be used for variables that fail tests of normality. Alpha level will be set at 0.05. Tukey *post-hoc* tests will be used to investigate significant interactions.

Lesion size and location (cortical/subcortical) will be used for secondary analyses regarding responders/non–responders, etc. (56–58) in which we used theory-based categorization of brain lesions to determine regions associated with better response to stroke rehabilitation, using a mixed-model analysis.

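### One of the four muscles in the intrinsic map total, extensor indicis (EI), is a forearm muscle, so the Aim 3 Muscle factor mixes its two levels

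*Protocol article*

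**What the plan says.** In the protocol article, the neurophysiological part of the Measures section lists ten muscles to be mapped by TMS, among them EI, written out as "extensor indicis longus [EI". It then forms two group totals, for "intrinsic muscles (FDI, EI, ADM, APB) and extrinsic muscles (FDS, EDC, FCR, ECR, EPL, and BR". These totals "will be calculated to quantify changes in cortical somatotopy of fine and gross motor muscle groups of the hand, respectively".

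The neurophysiological part of the Statistical Analysis section specifies a mixed model for Aim 3 with AREA as an outcome. One of its four fixed effects is "Muscle (Intrinsic, Extrinsic"; the others are test time, sensorimotor cortex and treatment group. Tukey tests are to follow up significant interactions at an alpha of 0.05. The article gives no definition of the two Muscle levels other than the lists in the Measures section, and no reason for placing EI with the intrinsic muscles.

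**The concern.** Intrinsic hand muscles are those whose bellies lie within the hand. FDI, ADM and APB meet that definition. Extensor indicis does not, because it is a forearm muscle acting on the index finger through a long tendon. This is ordinary anatomy and does not depend on any cited source. The article's own lists also show the inconsistency: EDC, the common finger extensor, and EPL, the long thumb extensor, are both extrinsic.

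The grouping defines a model factor. If it is applied as written, expansion confined to forearm muscles can appear partly as intrinsic expansion, and expansion confined to the intrinsic muscles can look smaller in relative terms than it is. Any statement that reorganisation was selective for one muscle group would rest on a mixed contrast.

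**Working it through.** **Inputs from the article.** The intrinsic total has 4 muscles (FDI, EI, ADM, APB) and the extrinsic total has 6 (FDS, EDC, FCR, ECR, EPL, BR). By count, EI is 1/4 = 25% of the intrinsic group. The article states no per-muscle map areas, no effect size or standard deviation for this contrast, and no power for Aim 3; the Sample Size section covers Aim 1 only. There is therefore no figure of the plan's own to reproduce. All changes below are assumptions, varied to show the range.

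**Scale.** The group measure begins "The total area representing the intrinsic muscles". The article does not say whether overlapping maps are summed or merged, or whether change is expressed in absolute or percent terms. Each of the first three scales below leads to a different statement.

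**1. Percent expansion.** Let gi and ge be the percent expansion of true intrinsic and true extrinsic muscles, let k be EI's map area relative to one intrinsic muscle, and assume that EI expands by ge.

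- Reported intrinsic expansion = (3·gi + k·ge)/(3 + k); extrinsic expansion = ge.
- Reported contrast = [3/(3 + k)]·(gi − ge), so the attenuation is k/(3 + k).
- k = 0.5: 0.5/3.5 = 14%. k = 1: 1/4 = 25%. k = 2: 2/5 = 40%.
- Example with k = 1: gi = 40%, ge = 0 is reported as 120/4 = 30% intrinsic expansion; gi = 0, ge = 40% is reported as 40/4 = 10% intrinsic expansion.

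**2. Average area change per muscle.** Let I, E and e be the area change of a true intrinsic muscle, a true extrinsic muscle and EI.

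- As planned: (3I + e)/4 − E. With EI moved: I − (6E + e)/7.

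| I | E | e | As planned | EI moved | Effect of the planned grouping |
|---|---|---|---|---|---|
| 1 | 0 | 0 | 0.750 | 1.000 | 25% smaller |
| 1 | 0.5 | 0.5 | 0.375 | 0.500 | 25% smaller |
| 1 | 0 | 0.5 | 0.875 | 0.929 | 5.8% smaller |
| 1 | 0 | 1 | 1.000 | 0.857 | 16.7% larger |
| 1 | 0.5 | 0.25 | 0.312 | 0.536 | 41.7% smaller |

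The 25% result appears when e = E. It shrinks when EI lies halfway between the groups and reverses when EI behaves like an intrinsic muscle.

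**3. Summed area change.**

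- As planned: 3I + e − 6E. With EI moved: 3I − (6E + e). Difference: 2e.
- I = 1, E = e = 0: 3 against 3, no change.
- I = 1, E = e = 0.5: 3 + 0.5 − 3 = +0.5 against 3 − 3 − 0.5 = −0.5, a change of sign.

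On this scale the error is a shift of twice EI's area change, not a proportional dilution.

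**4. Merged maps.** If overlapping maps were merged, EI's contribution would depend on its overlap with the other maps. The article gives no information on that, and EI could add little.

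**The case against.** **A functional grouping may have been meant.** The totals are described as representing fine and gross motor groups, and an index-finger extensor can plausibly be called fine. This is the best defence, but it does not settle the matter. EPL is also a forearm extensor of a single digit, and it sits in the other group without explanation. The analysis section carries only the anatomical labels. On the functional reading, the factor is misnamed and the placement of EI and EPL is inconsistent. What stands is that moving EI is not the only valid remedy.

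**A reader might infer that the contrast is diluted by a quarter in every case.** The documents do not support that. It needs a percent or averaged scale, equal map areas, and EI changing exactly as the other extrinsic muscles do. None of these is stated, and on summed area the proportional statement does not apply.

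**A reader might also infer that the Aim 3 hypothesis is compromised.** That goes too far. The hypothesis in Study Aims and Hypotheses concerns expansion of the ipsilesional hand representation, not a difference between intrinsic and extrinsic muscles. The two totals added together cover the same ten muscles wherever EI is placed. The analysis section names no particular interaction with Muscle; it refers to significant interactions in general.

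**The consequence is small.** This stands. MEP amplitude is estimated separately for each muscle, so regrouping loses nothing, and the outcome is secondary and mechanistic.

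**Conclusion.** The point holds as a classification error in a secondary analysis factor. One of the four muscles labelled intrinsic is extrinsic, and the comparable extensors EDC and EPL are on the other side, so the Muscle factor in the AREA model does not separate what its labels say.

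The documents do not fix the size of the bias. A 25% attenuation is the result under the simplest assumptions: percent or averaged scale, equal map areas, EI changing like the other extrinsic muscles. It is 14% to 40% if EI's map is half to twice the size of an intrinsic muscle's, with the other assumptions kept. On summed area it is a shift of twice EI's area change. If EI behaves like an intrinsic muscle, the planned averaged contrast is 16.7% larger than the regrouped one.

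This is a minor, worthwhile correction. It touches neither the ARAT analysis nor the sample size.

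**What to change.** Before the Aim 3 analysis, redefine the Muscle factor as:

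- intrinsic: FDI, ADM, APB;
- extrinsic: EI, FDS, EDC, FCR, ECR, EPL, BR.

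If a functional grouping was intended, rename the levels fine and gross in both the Measures and the Statistical Analysis sections, and place EI and EPL consistently with a stated reason.

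The choice should be recorded before the maps are compared between treatment groups, because a later choice could be steered by the results. The cost is a change to one grouping variable and the matching text; the per-muscle maps are already planned, so no new recordings are needed. The unequal number of muscles in the two groups is a separate matter, which this change does not address.

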##### Brain Connectivity

In an attempt to predict who will respond favorably to our therapeutic intervention, both Resting-State Brain Connectivity and Task-Based Brain Connectivity will be evaluated using EEG. Channels showing significant EEG desynchronization during the tasks will be identified and used in subsequent EEG connectivity analysis in Source Information Flow (SIFT) toolbox (54) to explore within-brain connectivity.

##### Experimental Conditions

The EEG-only experiments will be conducted prior to and immediately after the training, and at each of the three retention tests (see Table 2). Data will be collected (1) at rest, (2) during simple target-directed finger flexion/extension tasks of affected hand, and (3) during simple finger flexion/extension of unaffected hand with a randomized veridical or mirrored feedback of VR hand. In the resting task, 10 min of resting data will be collected while subjects are focusing their gaze on an object or cursor in the center of their visual field and relax for 10 min. In the affected hand movement task, subjects will wear data gloves that record finger joint angles. The joint angle data will be used in real-time to animate hand models presented on the computer screen. Data will be recorded as subjects perform 20 trials (5 s duration) of whole hand target-directed finger flexion and 20 trials of target-directed finger extension separated by 4–6 s of rest. The setup and trial durations are the same in the unaffected movement task, but visual feedback will randomly show two conditions, (1) veridical feedback, or (2) mirrored feedback. Due to the time limitations of inpatient participants, EEG-only experiments will be conducted using water-based caps (R-Net, Brain Products).

##### EEG Data Analysis

The EEG signals will be band-pass filtered (3–50 Hz) and decomposed into independent components using ICA. The resting state EEG data will be divided into non-overlapping 1-s epochs. The task-based EEG data will be divided into epochs that match the duration of task events. Data will be re-referenced offline to the mean signal of all 64 channels. Visual inspection will be done to remove EEG epochs and ICA components contaminated by muscle activity, or motion artifacts. The remaining ICA components will be transferred into channel space. Channel-based EEG connectivity will be studied using EEGLAB SIFT toolbox (54).

If stroke participants' MRI data is available, the stroke lesions will be mapped and a Boundary Element Model (BEM) will be created based on the subject's MRI image using FreeSurfer software, after masking out the mapped stroke lesion. Source Space data will be computed based on channel data and BEM using low-resolution brain electromagnetic tomography (LORETA) source localization method (55). Data will be extracted from selected regions of interests (ROIs) in the sensory, motor, premotor, visuomotor, and primary visual areas. Event-Related Spectral Perturbations (ERSPs) will be calculated for the selected ROIs. Between-ROI connectivity (BRC) in the brain will be quantified using normalized direct transfer function SIFT toolbox (54).

### Data Collection and Management

The assessment schedule is summarized in Table 2. Pre-post training assessments will take place at the KIR. The 1-month post therapy, 4 and 6-month post-stroke assessments will take place either at KIR, NJIT, or at Rutgers University. The clinical tests for all subjects will be assessed by an evaluator blinded to group assignment (see Table 2). Study data will be maintained in locked files and password protected computers. The code containing subject ID's will be maintained by the study coordinator.

### Sample Size

For Aim 1, the planned primary analysis method is a mixed effect model. The primary outcome measure is the change in ARAT score from baseline evaluated at 4 months post-stroke. The estimated effect size for the interaction term is 0.42 (Cohen's f), and the estimated within-subject correlation is 0.7. For testing the hypothesis of Treatment Group (EVR, DVR, UC, DMUC) ^*^Test Time (Baseline, 4 M post-stroke, 6 M post-stroke) effect, and assuming compound symmetry correlation for within-subject measurements, for significance level 0.05, a total of 84 patients (21 for each group) are needed to detect the overall Treatment Group ^*^ Test Time interaction effect. But for the main planned contrasts, Treatment Group (EVR, DVR) ^*^ Test Time (Baseline, 4 M post-stroke) and Treatment Group (UC, DMUC) ^*^ Test Time (Baseline, 4 M post-stroke), a total of 96 patients (24 for each group) are required to detect the effect size of 0.42 between EVR and DVR or between UC and DMUC over time. Since detecting these contrasts is the main goal of the study, at least 96 subjects, 24 subjects per group, are required. After taking into account subject attrition, our total sample size will be equal to 120. We plan to run an interim analysis and update the sample size when we have recruited 50% of subjects.

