### Statistical Analysis

The primary aim of the study is to test, at 4 months post-stroke, whether intensive VR/Robotic motor training initiated 5–30 days post-stroke, improves functional outcomes of the hemiparetic arm and hand when compared to VR/Robotic motor training initiated on 30–60 days post-stroke. Other comparsions include evaluating the type of training (EVR vs. DMUC) and dosing (DMUC vs. UC) initiated within 5–30 days post-stroke. The secondary aims will systematically investigate the mechanisms underlying the changes resulting from the early timing of training and increased dosing. Aim 2 will quantify the recovery and compensation profiles by examining the changes in kinematics and kinetics of the hand and arm associated with this training and Aim 3 will quantify patterns of cortical somatotopic reorganization and will investigate the relationship among these patterns of reorganization and the clinical and biomechanical outcomes.

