We will use the robust mixed effect model approach to analyze the data. We demonstrated in the past that this analytic approach is robust to detect treatment effects, even with relatively small groups of patients in whom within-group variance occurs with respect to stroke characteristics (56). Test Time (Pre, Post, 1-month post-treatment, 4 months post-stroke, 6 months post-stroke) and Treatment Group (EVR, DVR, DMUC, UC) will be treated as fixed effects in the mixed models. The interaction term between Test Time and Treatment Group will be included. Baseline measurements will be added as a covariate into mixed models for outcome variables. Random intercept will be used to model subject-level variation. Covariance pattern and model selection will be implemented with likelihood-based tests. Contrasts to compare group means will be applied to obtain comparisons between time, and between treatments, with multiplicity adjustment considered. We have an a priori interest in specific Test Time by Treatment Group interaction effects for the EVR-DVR, for the DMUC-UC, and for the EVR-DMUC comparisons. The particular differences we are interested in are Pre vs. Post and Pre vs. second (4 months post stroke) retention assessments. In the case of balanced data and equal variances, we will use the Tukey procedure to test for significant interaction effects, otherwise, Bonferroni correction will be used. In our design, the timing comparison is the difference between EVR and DVR. The dosage comparison is the difference between UC (usual care) and the DMUC (usual care plus 10 additional hours). In addition, we will be able to compare the type of training effect, VR vs. dose-matched usual care (EVR vs. DMUC), where both types of training are delivered in the same time period.

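### The 24 per group is calculated at an unadjusted 0.05, but the analysis section places EVR vs DVR under Tukey or Bonferroni and does not exempt it

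*Protocol article*

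**What the plan says.** **Sizing.** The Sample Size section gives the planning values: "The estimated effect size for the interaction term is 0.42 (Cohen's f), and the estimated within-subject correlation is 0.7". It sizes the overall group-by-time interaction first ("for significance level 0.05, a total of 84 patients (21 for each group) are needed"). It then sizes two pairwise contrasts from baseline to 4 months, EVR-DVR and UC-DMUC: "a total of 96 patients (24 for each group) are required to detect the effect size of 0.42 between EVR and DVR", and the same for UC and DMUC. These contrasts set the trial's size: "Since detecting these contrasts is the main goal of the study, at least 96 subjects, 24 subjects per group, are required". The total is raised to 120 for attrition. No power figure, sidedness or multiplicity allowance is given.

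**Testing.** The Statistical Analysis section declares a priori interest in interaction effects "for the EVR-DVR, for the DMUC-UC, and for the EVR-DMUC comparisons". It adds: "The particular differences we are interested in are Pre vs. Post and Pre vs. second (4 months post stroke) retention assessments". Tukey is to be used if the data are balanced with equal variances; "otherwise, Bonferroni correction will be used". An earlier sentence in the same paragraph says only that adjustment will be considered. The family over which the correction runs is not defined.

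**Primary aim.** Study Aims and Hypotheses and the opening of Statistical Analysis ("The primary aim of the study is to test, at 4 months post-stroke") single out EVR vs DVR. Both describe EVR vs DMUC and DMUC vs UC as other comparisons.

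**The concern.** The sizing rule and the testing rule cover the same contrast but use different significance thresholds. If the primary comparison has to pass a Tukey or Bonferroni threshold, 24 completers per group do not give the sensitivity that the sizing sentence implies. A true effect of the planned size would then be missed more often than the planners intended.

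The article also leaves open how many contrasts are confirmatory. The stated aim points to one, the sizing section to two and the analysis section to three. EVR-DMUC is hypothesised and tested but does not appear among the sized contrasts.

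**Working it through.** **Inputs.** From Sample Size: f = 0.42, significance level 0.05, 24 per group, 120 in total. From Randomization and Recruitment: equal allocation, 30 per group. From Statistical Analysis: three group contrasts and two time differences. Assumed: two-sided tests and an 80% power target.

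**Step 1: reproduce the plan's figures.** Use a noncentral F for the group-by-time interaction with λ = f²N.

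- Four groups × three times, N = 84: λ = 0.42² × 84 = 14.82, df 6 and 160, power 82.1%. N = 80 gives 79.7%, so 84 is the smallest multiple of four that reaches 80%.
- Two groups × two times, N = 48: λ = 0.42² × 48 = 8.47, df 1 and 46, power 81.3%. N = 46 gives 79.6%, so 24 per group is the smallest size that reaches 80%.

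Both stated sizes follow from this one convention at an unadjusted two-sided 0.05. Alternatives do not fit the pairwise figure: one-sided 0.05 gives 19 per group and 90% power gives 31. Building the 0.7 correlation in as λ = f²Nm/(1−ρ), with m the number of time points, gives 5.

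**Step 2: apply the corrections.** The 2 × 2 interaction equals a two-sample t-test on change with d = 2f = 0.84. At n = 24 the noncentrality is d√(n/2) = 0.84 × √12 = 2.91. Bonferroni uses t with 2(n−1) df. Tukey uses the studentized range for four groups with 4(n−1) df, divided by √2.

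| Rule for EVR-DVR | Per-test level | Critical t at n = 24 | Power, 24 per group | Power, 30 per group | n per group for 80% |
|---|---|---|---|---|---|
| Unadjusted | 0.05 | 2.01 | 81% | 89% | 24 |
| Bonferroni, 2 tests | 0.025 | 2.32 | 72% | 83% | 29 |
| Bonferroni, 3 tests | 0.0167 | 2.48 | 66% | 78% | 32 |
| Tukey, 4 groups | about 0.0104 | 2.62 | 62% | 74% | 34 |
| Bonferroni, 6 tests | 0.0083 | 2.76 | 56% | 70% | 37 |

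The two-test row corresponds to the two contrasts in the sizing section. The three-test row takes the three contrasts at 4 months. The six-test row is 3 contrasts × 2 time differences. The 30-per-group column assumes no dropout; going from 96 to 120 implies an allowance of 1 − 96/120 = 20%.

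**Step 3: allow for the baseline covariate.** The analysis model adjusts for baseline. If f describes the change score and the correlation is 0.7, the residual variance falls from 2(1 − 0.7) = 0.60 to 1 − 0.7² = 0.51 in units of the outcome variance. Then d rises to 0.84 × √(0.60/0.51) = 0.91. Power at 24 per group becomes about 80% (two tests), 75% (three), 70% (Tukey) and 65% (six). At 30 per group it is 89%, 85%, 82% and 78%.

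**The case against.** The strongest reply is that the article does not say the primary contrast is in the corrected family. It names one primary aim, says at one point only that adjustment will be considered, and leaves the family undefined, which an analysis plan could settle. Much of this stands. The six-test family is built by multiplying two statements of interest, and the 80% target is inferred. The power loss is therefore conditional. The conflict itself remains: the later sentence says a correction will be used, EVR-DVR is among the contrasts it governs, and nothing exempts it. Without baseline adjustment, any family of two or more takes 24 per group below 80%.

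A second reply is that the table is pessimistic because baseline adjustment and lower attrition would help. That is fair. With the covariate a two-test family is almost at 80% with 24 per group, and at 30 per group the three-test and Tukey cases pass 80%. This depends on f being defined on the change score, which the article does not say, and on few dropouts. The planned interim sample-size update might also help, but it is not described as dealing with multiplicity.

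Two stronger readings are tempting. A reader might infer that false positives are uncontrolled. The plan does adjust, so the consequence is lost power. A reader might also infer that the correction is chosen to suit the results. The choice between Tukey and Bonferroni is prespecified and depends on balance and variances, not on treatment effects or p-values.

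**Conclusion.** The point holds in conditional form. The 24 per group is right for an unadjusted two-sided 0.05 and is not right under the correction that the analysis section states. If EVR-DVR is inside the corrected family, power at f = 0.42 with 24 completers per group falls from about 81% to between 72% and 56%, depending on the family. Part of that loss is recoverable through the baseline covariate. Full retention of 30 per group restores 80% for a family of two (83%), but without the covariate it does not do so for three tests (78%) or six (70%).

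This rests on an inferred 80% target, two-sided testing, and f applied to the change score with λ = f²N, the convention that reproduces both published sizes. The 56% needs the further assumption that both time differences count, and should not be quoted as the plan's power. The type I error of the primary result is not called into question.

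**What to change.** In Statistical Analysis, state that EVR vs DVR on ARAT change at 4 months is the single primary test at two-sided 0.05 and lies outside the Tukey/Bonferroni family. State that the multiplicity adjustment applies to the remaining contrasts (DMUC-UC and EVR-DMUC) and time differences, by a prespecified Bonferroni or Holm procedure or a fixed sequence. The order of any sequence is for the investigators to choose.

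In Sample Size, say that 24 per group gives about 81% power for EVR vs DVR at f = 0.42 and two-sided 0.05, and that power for DMUC-UC and EVR-DMUC is lower and is given at their adjusted level. For example, if Bonferroni covers only those two contrasts at 4 months, each has about 72% power at the same f and 24 per group.

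This needs no extra patients, but it is more than a change of wording. DMUC-UC, now called a main planned contrast, is no longer covered by the 24-per-group claim at 0.05. If the investigators want to keep it on an equal footing with EVR-DVR, the alternative is to size at the adjusted level. Without the baseline covariate that means 29 completers per group for a family of two, 32 for three, 34 for Tukey or 37 for six. At the implied 20% attrition, enrolment would be 116/0.8 = 145, 128/0.8 = 160, 136/0.8 = 170 or 148/0.8 = 185, against 120 planned.

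### The 24 per group reproduces only at an unadjusted 0.05, but the analysis tests the same contrasts with Tukey or Bonferroni correction, which lowers power in every plausible family

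*Protocol article*

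**What the plan says.** The Sample Size section of the protocol article gives these planning inputs: "The estimated effect size for the interaction term is 0.42 (Cohen's f), and the estimated within-subject correlation is 0.7". For the overall Treatment Group by Test Time interaction it says "for significance level 0.05, a total of 84 patients (21 for each group) are needed". For the EVR-DVR and UC-DMUC contrasts from baseline to 4 months it says "a total of 96 patients (24 for each group) are required to detect the effect size of 0.42 between EVR and DVR", and it applies the same number to the UC-DMUC contrast. It lets these contrasts set the size of the trial: "Since detecting these contrasts is the main goal of the study, at least 96 subjects, 24 subjects per group, are required". It then adds "After taking into account subject attrition, our total sample size will be equal to 120" and announces an interim analysis with a sample-size update at 50% recruitment. The section states no power and mentions no multiplicity adjustment.

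The Statistical Analysis section declares an a priori interest in three group-by-time contrasts (EVR-DVR, DMUC-UC and EVR-DMUC), each for two time differences (Pre to Post, and Pre to 4 months). It says that, with balanced data and equal variances, "we will use the Tukey procedure to test for significant interaction effects, otherwise, Bonferroni correction will be used". It also says that baseline will enter the mixed models as a covariate. It does not give the size of the correction family, and it does not say that EVR-DVR is tested at the full 0.05.

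**The concern.** A required sample size is tied to the critical value of the test it serves. Here the number of patients is derived at 0.05, while the analysis commits the same contrasts to a stricter threshold. If both sections stand as written, the 96 belongs to a test that the plan does not intend to run.

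What is at stake is how a non-significant result would be read. The 96 is the figure on which the article rests its ability to meet its main goal. If power for an effect of the planned size is lower than the sizing implies, a null finding on timing or dosing could be taken as stronger evidence of no difference than it is. The interim sample-size update also needs a defined alpha to work from.

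**Working it through.** **Inputs.** From Sample Size: f = 0.42, alpha 0.05, within-subject correlation 0.7 with compound symmetry, 24 per group, 120 enrolled. From Statistical Analysis: three group contrasts, two time differences, Tukey or Bonferroni, baseline covariate. Assumed: two-sided testing and 80% target power.

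**Step 1: reproduce the plan's figures.** Use the noncentral F with λ = f²N.

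- Overall interaction, 4 groups by 3 times: df = 3 × 2 = 6 and 2(N − 4). At 21 per group, N = 84, λ = 0.1764 × 84 = 14.82, df 6 and 160, power 0.821. At 20 per group it is 0.797. The smallest n reaching 80% is 21, as printed.
- One contrast between two arms: df = 1 and N − 2. At 24 per group, N = 48, λ = 0.1764 × 48 = 8.467, df 1 and 46, power 0.813. At 23 per group it is 0.796. The smallest n reaching 80% is 24, as printed.

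Both printed figures therefore come out at unadjusted 0.05 and 80% power. If f is instead given the repeated-measures noncentrality f²Nm/(1 − ρ), with m time points and correlation ρ, power at 24 per group is close to 100%. That is not the basis used.

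**Step 2: apply the planned correction on the same basis.** For Bonferroni, repeat the contrast calculation at 0.05/k. For Tukey, the critical |t| is q(0.95; 4, 92)/√2 = 3.700/1.414 = 2.617, with noncentral t and δ = √8.467 = 2.91.

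| Test of the contrast | Power, 24 per group | n per group for 80% | Total | f detectable at 80%, 24 per group |
|---|---|---|---|---|
| Unadjusted | 0.813 | 24 | 96 | 0.413 |
| Bonferroni, 2 tests | 0.722 | 29 | 116 | 0.458 |
| Bonferroni, 3 tests | 0.6645 | 32 | 128 | 0.482 |
| Tukey, 4 arms | 0.616 | 34 | 136 | 0.500 |
| Bonferroni, 6 tests | 0.564 | 37 | 148 | 0.522 |

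Totals are evaluable patients before any allowance for attrition. The Bonferroni rows keep the two-arm 46 df that reproduces the 24. With four-arm df of 92 they become 0.735, 0.681 and 0.586.

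**Step 3: credit the baseline covariate.** Suppose f is on the change-score scale. With unit variance and correlation 0.7, the change score has variance 2(1 − 0.7) = 0.60, and the baseline-adjusted outcome has residual variance 1 − 0.7² = 0.51. The noncentrality grows by 0.60/0.51 = 1.176, so λ = 8.467 × 1.176 = 9.96. With four-arm error df (96 − 4 − 1 = 91; 92 for Tukey), power at 24 per group is:

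- unadjusted 0.88
- Bonferroni over two 0.81
- Bonferroni over three 0.76
- Tukey 0.70
- Bonferroni over six 0.68

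**Step 4: no attrition, 30 per group.** Without the covariate, power is 0.83 (two tests), 0.78 (three), 0.74 (Tukey) and 0.70 (six). With the covariate it is 0.89, 0.86, 0.82 and 0.80.

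**The case against.** The printed numbers are not miscalculated. Both 84 and 96 follow exactly from the stated alpha and effect size. This stands: the fault is a mismatch between two sections, not an arithmetic slip.

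A reader might infer that the trial simply has 56-67% power under its stated tests. The article does not support that, for three reasons.

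- That range leaves out the two-contrast family that the Sample Size section itself sized, for which power is 72%.
- Its low end needs the Pre-Post differences to share a family with the 4-month differences, and nothing in the article fixes that.
- It ignores the planned baseline covariate, with which the adjusted figures run from 68% to 81%.

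For the same reasons, the article does not show that all 120 patients without attrition would still fall short of 80%. That depends on the family and on whether the covariate is credited. Nor can one say that the interim update starts from a wrong alpha, because no alpha is given for it. The 81% is also not a claim of the article.

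It can further be said that EVR-DVR at 4 months is the single primary aim, that the article first speaks only of multiplicity adjustment being considered, and that an analysis plan may settle the family. But the later sentence commits to one correction or the other and covers both cases, and no contrast is exempted. The point is not that detail is missing: two statements in the same article do not fit together.

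**Conclusion.** The concern holds as a misalignment. The 24 per group rests on an unadjusted 0.05, while the contrasts it serves are to be tested with Tukey or Bonferroni correction, and every family considered lowers their power.

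For the three comparisons named in the Statistical Analysis section, power at 24 per group is about 66% (Bonferroni) or 62% (Tukey) against 81% on the sizing basis. With the baseline covariate credited it is about 76% or 70% against 88%. Only the two-contrast family with the covariate credited reaches 80%, at about 81%, and the Sample Size section does not claim that gain.

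These figures assume two-sided tests, an inferred 80% target, f = 0.42 on the change-score scale, correlation 0.7 under compound symmetry, and 24 evaluable per group. The exact loss cannot be fixed until the family is named.

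**What to change.** Bring the two sections into line. Restate the sample-size sentence at the alpha and model with which the contrasts will be tested. Name the correction family (which contrasts, and whether Pre-Post is included) and say whether the baseline covariate is credited. Then give the resulting power at 24 evaluable per group or the detectable effect. For example, with Bonferroni over three contrasts and no covariate credit, power is about 66% for f = 0.42 and the effect detectable at 80% is f of about 0.48. State the target power, and use the same alpha in the interim sample-size update.

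The cost is one rewritten sentence and a less favourable stated figure. No extra patients are requested and trial conduct does not change.
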